## Methods

### Study Design

This study is registered with the Australian and New Zealand Clinical Trials Registry (ANZCTR), which is a primary registry in the World Health Organization Registry Network (registration number: ACTRN12619001302145p).

A multiple baseline across-individuals design will be employed. Multiple baseline designs in mental health intervention studies are those where a baseline period of stability of symptoms is established before the intervention is introduced. In this way, each participant acts as their own control, and internal validity is demonstrated when there is no change in symptoms until after the treatment is introduced [18]. In the design to be used in this study, all participants commence the baseline period at the same time but start the treatment at different times after a minimum number of daily data readings (at least 20) have been received. This sequential commencement approach further strengthens the internal validity by reducing the likelihood of history, maturation, or other extraneous factors explaining any observed emotional or behavioral change that occurs simultaneously with the introduction of the treatment. The multiple data recordings allow for the use of analytical techniques such as a time series analysis [20,26] and will involve participants reporting ratings of subjective units of distress (SUDS) via SMS text messaging using a 10-point scale. In this design, 4 or more baselines are recommended [18,20], and these will follow the pattern shown in Figure 1.

**Figure 1 figure1:**
[figure not shown]
Overview of the proposed study design.

This research will use a *prescribed dosage* approach, as if the app was a *digital antidepressant*: one 10-min *dose* of app use per day for 5 days per week. The 10-week intervention period creates equivalence with one 50-min session per week for 10 weeks, which is the annual maximum number of psychology sessions rebated under Australia’s Medicare system [27]. The rationale for a minimum 3-week postintervention period (to demonstrate the stability of the treatment effect) is similar to that described earlier, namely, that 20 daily SUDS ratings are needed for a valid data analysis. The justification for using the 5 chosen apps are as follows: (1) each has some evidence of efficacy published in a peer-reviewed journal, (2) all have publicly available free versions, and (3) all can fit the *prescribed dosage* approach. The chosen apps use 3 popular evidence-based frameworks employed across mental health settings for treating anxiety and/or depression: cognitive behavioral therapy (CBT), mindfulness, and positive psychology. Finally, the rationale for using 10 participants per app is that, even accounting for a 50% to 60% attrition rate [28], approximately 3 to 5 participants per app will provide enough data for a valid statistical analysis using time series conventions. As previously noted, this number of replications in a single-case design with similarly presenting individuals can produce robust and generalizable findings if the results are comparable in each case [18-20].

### Recruitment

Commencing in January 2020, participants will be recruited throughout Australia by advertising the proposed study to nongovernment organizations that run programs for clients with mental illness (eg, the Benevolent Society), contacting associations of mental health professionals that may alert their members to the proposed study (eg, Australian Psychological Society), and contacting support groups and other organizations in the mental health sector (eg, Mental Health Victoria), requesting they advertise the proposed study on their various social media platforms. The advertisement is shown in Multimedia Appendix 1. Recruitment will cease once 50 participants are recruited. Owing to the nature of the proposed study design, new participants cannot commence after the study has started because the multiple baseline design requires participants to begin at the same time and then have specifically staggered phase commencements after that. Figure 1 demonstrates this process.

All 50 participants (10 for each app) will be randomized to an app and their position in the single-case design (ie, P1 to P10) using the web-based random number generator, *Research Randomizer* [29]. The full inclusion and exclusion criteria are presented in Textboxes 1 and 2, respectively. A financial reimbursement will be offered to participants of Aus $0.50 (US $0.33) per daily SUDS rating sent via a text message. The researchers acknowledge that financial payments have the potential to interfere with ecological validity, because a person in the community would not normally be paid for using a mental health app, and intrinsic motivation, because people could potentially use the app for the benefit of financial remuneration rather than for the value of improving their mental health. However, the low amount of remuneration being offered of approximately Aus $45.00 (US $29.41) on average is not considered payment for participation in the proposed study but rather reimbursement of personal expenses incurred while taking part in the proposed study. Given that the effectiveness of mental health apps has the potential to benefit those from low socioeconomic groups, being reimbursed for providing in excess of 80 text messages will alleviate reasons that a potential participant of lower socioeconomic background could provide for being out of pocket for the cost of sending text messages from their mobile phone. Therefore, it is envisaged that prospective participants will more likely have motivation to improve their mental health beyond receiving financial remuneration. In addition, this financial incentive will not be advertised, and participants will only learn about this when they provide consent when completing the demographics questionnaire.

Study eligibility: inclusion criteria.Inclusion criteria:18 years of age or olderAbility to read EnglishHave access to a smartphone or tablet device capable of connecting to the internet and downloading the required app and sending and receiving SMS text messagesAgreeable to providing daily subjective units of distress ratings via SMS text messages and to completing self-report measures at 5 different time points (including 6-month follow-up)Mild-to-moderate anxiety and/or depression, diagnosed by a qualified health professional and confirmed by the researchers (all of whom are clinical psychologists) after screening. Screening involves analyzing the participants’ scores on the first completed set of outcome measures: the Depression Anxiety Stress Scale-21 short-form version and the Outcome Questionnaire-45 second edition version. For more information on these, see the *Mental Health and Well-Being* subsection.

Study eligibility: exclusion and removal criteria.Exclusion criteria:Severe anxiety and/or depression, as indicated by the initial outcome measures and in any responses to specific questions in the demographics questionnaireHistory of psychosis or other complex mental health presentation as deemed by the researchers to be unsuitable for participation in this research. There will be a question in the demographics questionnaire that asks participants for their complete mental health diagnosesCurrent suicidal ideation, as indicated by a participant’s responses on the initial outcome measuresRemoval criteria:Not providing any subjective units of distress rating for a 2-week periodNot providing a minimum of 20 subjective units of distress ratings in the baseline and postintervention phases or a minimum of 40 subjective units of distress ratings in the intervention phaseNot completing outcome measures either preintervention or postinterventionClinically significant/unsafe decline in mental health as indicated by subjective units of distress ratings or outcome measures or in the judgment of researchersSuicidal ideation

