#### Time Series Analysis

A process for conducting time series analyses for psychological research was described by Borckardt et al [59] using the *R* statistical software package. In the proposed study, the commencement of the intervention will be the predictor in a regression model that uses data before and after this point to determine if there has been a statistically significant impact on subjective distress, as measured by SUDS ratings. A minimum of 20 data points are required in each phase [20,26]. The *R* statistical package will use conventions of autoregressive integrative moving average (ARIMA) modeling to account for autocorrelated data [60] when building the model.

The time series analyses [59] will evaluate statistically significant changes across the phases of the proposed study. Overall level and trends across time will be considered, and if necessary, adjustments will be made for irregular variation effects. An *irregular factor* is similar to the error terms used in many statistical models, such as generalized linear modeling. The methods of making such adjustments differ depending on the nature of the collected data but may include the augmented Dickey-Fuller test, Durbin-Watson test and/or the Ljung-Box test as part of an ARIMA model.

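### The eligibility list called full does not address current use of the five free apps or changes in other care, so one person's baseline may not be app-free and another's change may be wrongly credited to the app

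*Protocol article*

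**What the plan says.** Under Recruitment the article says "The full inclusion and exclusion criteria are presented in Textboxes 1 and 2, respectively". The exclusions are severe symptoms, psychosis or another complex presentation, and current suicidal ideation. Removal rests on missing ratings or questionnaires, clinical decline, or suicidal ideation. The researchers' discretion concerns the clinical presentation. No criterion refers to use of the five apps, to other mental health apps, or to starting, stopping or changing other care.

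Entrants must have "Mild-to-moderate anxiety and/or depression, diagnosed by a qualified health professional and confirmed by the researchers". One recruitment route is "nongovernment organizations that run programs for clients with mental illness"; others are professional associations and support groups. Of the apps, Study Design says "all have publicly available free versions". Participants are randomized to an app and to a start position, with no stated reference to what they already use.

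The validity argument in Study Design is that "each participant acts as their own control, and internal validity is demonstrated when there is no change in symptoms until after the treatment is introduced". Under Time Series Analysis, "the commencement of the intervention will be the predictor in a regression model that uses data before and after this point". The clinical significance and reliable change indices (CSI and RCI) are pre-to-post comparisons within one person.

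**The concern.** An own-control design reads the difference between phases as the effect of the app. That needs two conditions for each person: the app is absent in baseline, and nothing else that bears on symptoms changes at about the same time. The plan secures neither by eligibility, allocation or a stated analysis step.

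The two failures act in opposite directions. If the assigned app is already in use during baseline, its effect is in both phases and the contrast shrinks towards zero. If other care changes during the 10-week phase, its effect falls on the intervention side of the contrast and can look like an app effect.

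Study Design expects about 3 to 5 analysable people per app and rests generalization on their results being comparable, so a single affected case is a sizeable share of the evidence for that app.

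**Working it through.** **1. The plan's own figure.** Inputs from Study Design: 10 participants per app, attrition 50% to 60%, about 3 to 5 analysable. Completers = 10 × (1 − attrition): 10 × 0.5 = 5 and 10 × 0.4 = 4. The lower end of 3 would need 70% attrition, but as an approximate range the statement reproduces. I use n = 4 below.

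**2. Which safeguards cover which threat.**
- *Staggered, randomized starts* protect against events that affect everyone at the same calendar time. They do not protect against one person's own change of care, because the time series, RCI and CSI analyses are per person.
- *A stable baseline before the app starts* copes with care that is ongoing and steady. It does not detect existing use of the assigned app, which may itself look stable, and it cannot prevent a change after baseline.
- *The time series model* names the start of the intervention as its predictor and no term for other care.

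**3. Chance that an app's completers include an affected case.** The documents give no frequency. Assume each completer is independently affected, by either route, with probability p of 10% to 20%.

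P(at least one of n) = 1 − (1 − p)^n
- p = 0.10, n = 4: 1 − 0.9^4 = 1 − 0.656 = 34%
- p = 0.20, n = 4: 1 − 0.8^4 = 1 − 0.410 = 59%

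P(at least two of 4) = 1 − (1 − p)^4 − 4p(1 − p)^3
- p = 0.10: 1 − 0.656 − 0.292 = 5%
- p = 0.20: 1 − 0.410 − 0.410 = 18%

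**4. How much of p current app use can supply.** With five apps allocated at random, a user of one of them draws that same app about one time in five. For this route alone to give p = 10%, about 0.10 / 0.20 = 50% of the sample would have to be using one of the five. Any p of this order would therefore have to come mostly from changes in other care.

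**5. What an affected case does to the SUDS analysis.** Illustrative simulation of one participant: 20 baseline and 70 intervention days, regression on phase with first-order autoregressive errors, assumed SD 1.5 and autocorrelation 0.3, 1,500 series per row.

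| Scenario | Mean estimated app effect | Significant at 5% |
|---|---|---|
| No app effect, no other change | 0.01 | 4.9% |
| No app effect; other care lowers SUDS by 1.5 from 10% into the phase | −1.28 | 64% |
| Same, from 30% in | −1.00 | 37% |
| Same, from 50% in | −0.71 | 20% |
| App effect −1.5, app-free baseline | −1.51 | 82% |
| App effect −1.5, already present in baseline | 0.00 | 6.5% |

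Both directions appear. The SD, autocorrelation and effect sizes are assumptions, so the table shows the mechanism and not the expected size in this trial.

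**The case against.** The strongest reply is that the consequences are easily overdrawn. Most of that reply stands, and four stronger readings should be set aside.

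- *That past app use or any concurrent care spoils the baseline.* A reader might infer this from the recruitment routes and the diagnosis requirement. Those make ongoing care likely but say little about changes in care, and the own-control design largely handles care that stays the same. Past users must still have mild-to-moderate symptoms at entry. The direct problem is current use of the assigned app.
- *That anyone who starts other care is counted as an app success.* In the simulation 36% to 80% of such series are not significant, depending on timing. The plan also considers trend and inspects up to 112 daily ratings, so a shift some weeks after the app starts may be visible. The pre/post RCI has no such protection.
- *That one or two affected cases decide an app's verdict.* The article sets no verdict rule and admits under Limitations that generalization may fail if outcomes differ.
- *That neither factor is recorded.* The questionnaire topics named in the text omit both, but that list is not presented as complete, the form itself is in Multimedia Appendix 3, and researchers may contact participants for more information. Treatment and app history may be asked.

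It can also be said that broad eligibility suits the stated aim of testing under real-world conditions. That is a reason not to exclude such people. What remains is that the list is described as full, and that recording a factor, even if the form does so, supplies no rule for allocation or reporting.

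**Conclusion.** The concern holds in a limited form. The stated criteria and allocation allow a participant to be assigned an app already in use, and the stated analyses have no step that separates a person's own change of care from the app. The first hides an effect and the second can create one. Staggered starts and a stable baseline protect against neither.

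The size of the bias cannot be known from the documents. The 34% to 59% (at least one of 4) and 5% to 18% (at least two of 4) rest on an assumed, independent 10% to 20% per participant that pools two biases of opposite sign. They are chances that a case is affected, not chances that a conclusion is wrong. The omission is worth correcting because the remedy is cheap and the number of cases per app is small; it does not invalidate the design.

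**What to change.** 1. **Before randomization (Phase 1):** ask about current and recent use of each of the five apps, if the form does not already. Randomize each participant only among apps not currently in use, before baseline, keeping 10 per app and the random start positions.
2. **At each later questionnaire point:** add one dated yes/no item on starting, stopping or changing therapy, medication or another mental health app. Naming other apps matters because Phase 4 gives participants information on all five.
3. **In the analysis:** keep every case in the main report. Flag those with a change between the pre and post questionnaires, mark the date on the SUDS plot, and give each app's replication count with and without the flagged cases. Dropping flagged cases outright would be a post-randomization exclusion, possibly selective if people change care because the app is not helping.

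Cost: two short items in existing online forms, an ethics notification, a slightly constrained randomization, and a replication count that may look less favourable for some apps. Nobody is excluded and nobody's care is restricted.

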#### Phase 3 (Intervention)

Participants are provided with generic instructions for all apps, links to both the Apple App Store and Google Play Store for their app, and specific instructions on how to use their app once it is downloaded (Multimedia Appendix 2). In addition, website links to information on the type of evidence-based framework their app uses and emergency contact information in the event of a mental health crisis are provided. Participants continue to supply daily SUDS ratings for the minimum 10-week intervention. Data analysis will be ongoing throughout this phase and will be used to assist in determining whether any participant’s mental health is significantly deteriorating. If a participant provides a SUDS rating of 10 for 2 consecutive days, they will be contacted for a check on their welfare. Similarly, if a participant’s SUDS ratings are above 8 for 5 consecutive days, they will also be contacted for a check on their welfare. We have chosen these cutoff values because the information provided to participants about the SUDS indicates that 8 is equal to their perception of feeling *very distressed* and 10 is equal to their perception of feeling the *worst distress.* The SUDS does not have a universal categorization label for each point on the scale, in addition to the number. Instead, it was designed to allow flexibility in an individual’s self-assessment [57] and labeling can vary from study to study. The mental health and well-being outcome measures (DASS-21 and OQ-45.2) and uMARS are completed at the end of this phase. If a participant’s responses on the outcome measures reveal a clinically significant decline in mental health compared with their responses at the beginning of the intervention, which places them in a severe category of mental illness, she/he will be contacted for a check on their welfare. In all cases, if a participant is categorized as being inappropriate for continuation in the proposed study, she/he will be directed toward more appropriate forms of care.

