#### Clinical Significance and Statistical Reliability

Meaningful or clinically significant changes occur when an individual is in the dysfunctional (clinical) range at the commencement of treatment and in the functional (nonclinical) range at the end of treatment [61,62]. The clinical significance index (CSI) indicates whether individuals have made meaningful improvements to their emotional health and moved from being clinically dysfunctional to functional [63]. The reliable change index (RCI) verifies the statistical significance of any change in an individual’s score from pre- to postintervention [62]. This approach is particularly useful for single-case designs because it allows researchers to focus on individual functioning [64] and to adjust treatment if necessary. Jacobson and Truax [62] developed a classification system to describe the change in a participant’s mental health in a study’s conclusion: *recovered*=clinically significant and statistically reliable; *improved*=not clinically significant, but statistically reliable; *unchanged*=not clinically significant or statistically reliable; and *deteriorated*=clinically significant and/or statistically reliable in a worsening direction.

To determine the CSI, a cutoff point between the scores obtained by the functional and dysfunctional populations on a particular measure is identified [61,62]. Scores on either side of this point are statistically more likely to indicate whether an individual is functional or dysfunctional [61,62]. Normative data are required for both functional and dysfunctional populations for the measures being used. The CSI is based on the following formula [62]:

where 1 represents the nonclinical population and 2 represents the clinical population.

The RCI is a function of a measure’s standard deviation and reliability [61]. It measures an individual’s change in self-reported score from pretreatment to follow-up for statistical reliability. If an individual’s change exceeds 1.96 times the SE, the change is statistically reliable at *P*<.05 because it is unlikely to occur more than 5% of the time as a result of measure discrepancy or chance [61]. The RCI is calculated as follows [62]:

where S_diff_=√2(S_E_)^2^ and S_E_=*SD* of both groups×(√1−test-retest reliability).

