#### Data Exclusion

Data will be excluded from time series and visual analyses if a participant fails to provide a minimum of 20 SUDS ratings in phase 1 (baseline) and/or phase 4 (postintervention) and 40 SUDS ratings in phase 3 (intervention). Data will be excluded from CSI and RCI analyses if a participant fails to complete baseline and/or postintervention mental health and well-being outcome measures (DASS-21 and OQ-45.2). Owing to the nature of the proposed study design, participants who dropout because they did not provide the required minimum data cannot be replaced by new participants once the baseline phase has commenced.

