### Limitations and Strengths

This study has some limitations. First, it may not be possible to generalize the findings if the outcomes for participants with the same condition differ in significant ways. Second, there is no certainty that participants will provide daily SUDS ratings for 16 weeks, despite the minimal effort involved. Third, with many brands of smartphones using different versions of software, there is a risk that the technology between phone and app may not be compatible for some participants.

This study also has several strengths. By using questionnaires that consider subject distress, symptoms, and life functioning at different time points, the design allows for a comprehensive approach toward the impact of the apps. The use of the DASS-21 and OQ-45.2 questionnaires at multiple time points will allow an examination of issues such as suicidality, dysfunctional coping activities (such as excessive alcohol consumption), physical health, and sleep disturbance. The single-case design will also provide in-depth information about individual responses and offers a way that clinicians may be able to contribute to the evaluation process (see the Conclusions section). Finally, there is the ambitious goal of offering a future methodology that could be applied to larger RCTs via a highly digitized procedure.

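### Participants removed for decline during the intervention fall out of every outcome analysis, so deterioration is under-counted and each app's results lean toward benefit

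*Protocol article*

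**What the plan says.** The exclusion and removal criteria (textbox in Recruitment) list clinically significant or unsafe "decline in mental health as indicated by subjective units of distress ratings or outcome measures" among the grounds for removal; researcher judgment is a further trigger. Suicidal ideation is a separate ground.

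Data Exclusion sets two filters:
- For clinical significance and reliable change: "Data will be excluded from CSI and RCI analyses if a participant fails to complete baseline and/or postintervention mental health and well-being outcome measures".
- For the SUDS series: "Data will be excluded from time series and visual analyses if a participant fails to provide a minimum of 20 SUDS ratings" in baseline or postintervention, or 40 in the intervention phase.

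Clinical Significance and Statistical Reliability defines four outcome classes for each participant. The fourth, *deteriorated*, is change that is "clinically significant and/or statistically reliable in a worsening direction".

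Phase 3 (Intervention) describes monitoring while the app is in use. Ongoing analysis "will be used to assist in determining whether any participant’s mental health is significantly deteriorating", and certain SUDS patterns lead to a welfare check. For a decline on the end-of-phase questionnaires "which places them in a severe category of mental illness, she/he will be contacted for a check on their welfare". Stopping is then conditional: "if a participant is categorized as being inappropriate for continuation in the proposed study, she/he will be directed toward more appropriate forms of care".

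In Phase 4 (Postintervention) the DASS-21 and OQ-45.2 are taken only after at least 20 further SUDS ratings. Nothing in the article says how a participant removed for decline is classified or counted.

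**The concern.** The event that triggers removal is much the same event that the *deteriorated* class is meant to record. Removal cuts off the data that Data Exclusion requires, so exclusion from analysis depends on the outcome and works in the app's favour.

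Research question 1 asks whether the apps give clinically significant improvement. The Study Design section rests generalisability on about 3 to 5 cases per app showing comparable results. If worsening cases are the ones that disappear, the remaining cases look more alike and more favourable than the people who were given the app. With so few cases, one missing deterioration can change what is concluded about an app. Participants lost for want of data cannot be replaced, and Limitations and Strengths does not mention this selection.

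**Working it through.** **Step 1: the plan's own figure.** Study Design gives 10 participants per app and 50% to 60% attrition. Then 10 × (1 − 0.50) = 5 and 10 × (1 − 0.60) = 4, consistent with the stated figure of approximately 3 to 5 analysable participants.

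**Step 2: follow one participant.** Suppose someone starts the app, worsens, and is removed partway through Phase 3.
- *Questionnaires.* The DASS-21 and OQ-45.2 are scheduled before baseline, at the end of baseline, at the end of Phase 3, after the Phase 4 SUDS ratings, and at 6 months. This person has only the first two, both from before the app. On any definition of postintervention that measure is missing, so the person is out of the clinical-significance and reliable-change analyses.
- *SUDS.* There are no Phase 4 ratings, so the postintervention minimum of 20 is not met, and the Phase 3 minimum of 40 may not be met either. The person is out of the time series and visual analyses.
- *Rescue.* No section brings the person back by classification, by last available measure, or as a reported count.

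**Step 3: where the text is unclear.** Someone who completes the end-of-Phase-3 questionnaires and is then removed is lost to the questionnaire analyses only if postintervention means Phase 4. Phase 4 carries that label. Yet the clinical-significance section refers to the functional range at the end of treatment, and describes reliable change once as pre- to postintervention and once as pretreatment to follow-up. The time point is not fixed.

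**Step 4: illustrate the size.** The article gives no deterioration rate, so every input here except *N* is assumed. Let *N* = 10 per app, *r* = 4 truly improved, *D* = truly deteriorated, *s* = share of deteriorators removed before a usable post-measure, and no other attrition.
- Improved share seen = *r* / (*N* − *sD*)
- Deteriorated share seen = (1 − *s*)*D* / (*N* − *sD*)

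| *D* | None removed: improved / deteriorated | Half removed | All removed |
|---|---|---|---|
| 1 | 4/10 = 40% / 10% | 4/9.5 = 42% / 0.5/9.5 = 5% | 4/9 = 44% / 0% |
| 2 | 4/10 = 40% / 20% | 4/9 = 44% / 1/9 = 11% | 4/8 = 50% / 0% |
| 3 | 4/10 = 40% / 30% | 4/8.5 = 47% / 1.5/8.5 = 18% | 4/7 = 57% / 0% |

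Fractional counts are expectations.

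**Step 5: on the expected number of cases.** If the 50% to 60% attrition is unrelated to outcome, the shares stay the same in expectation. With an assumed 20% deterioration rate, 4 to 5 retained participants would include 4 × 0.2 = 0.8 to 5 × 0.2 = 1.0 deteriorated case per app if nobody is removed for decline, and none if all such participants are.

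**The case against.** The best defence is that removal is not automatic and that exclusion follows missing data, not removal as such. Phase 3 puts a welfare check first and makes stopping a judgment. A participant with mild-to-moderate symptoms can worsen reliably without being removed, finish, and be classed as *deteriorated*. Worsening can also first appear at the end of Phase 3, in Phase 4 or at 6 months. All of this stands. A reader might infer that the *deteriorated* class is emptied by design, or that harm cannot appear in an app's results. The documents do not support either; depletion and under-counting are what they show.

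Nor do they support the inference that anyone whose end-of-Phase-3 questionnaires show decline is necessarily excluded. The stated response is a welfare check when the decline reaches a severe category, and what happens to the data depends on the undefined time point.

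A reader might also see a contradiction with the claim that repeated questionnaires "will allow an examination of issues such as suicidality". That is weak: detecting new ideation at those time points is such an examination, and it is compatible with removal afterwards.

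Finally, the plan specifies individual analyses and states no percentage improved per app, so the shares above are a device for showing direction and not a planned endpoint.

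None of this answers the core point. Whoever is removed for decline during the intervention, by judgment or otherwise, has been selected on the outcome and is lost to all these analyses.

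**Conclusion.** The point holds in limited form. The stated rules make exclusion depend on deterioration for participants removed during the intervention. They deplete the *deteriorated* class, under-count harm, and tilt results on about 3 to 5 cases per app toward benefit.

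The direction follows from the text; the size does not. It depends on how many participants deteriorate and what share of them is removed, and the article gives neither. Under the assumptions above the improved share is overstated by 2 to 7 percentage points if half the deteriorators are removed, and by 4 to 17 points if all are. With few or no removals for decline, the effect is small or absent.

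**What to change.** Leave the clinical removal rules as they are and change the analysis. The removal criteria, Phase 3, Clinical Significance and Statistical Reliability, and Data Exclusion need to be reconciled as follows:

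1. State whether postintervention means the end-of-Phase-3 or the Phase 4 measure. Where Phase 4 scores are missing because of removal, use the end-of-Phase-3 scores for clinical significance and reliable change.
2. Count removal for decline or suicidal ideation after app start as an unfavourable outcome for the assigned app. Show it as a separate *removed for decline* category beside recovered, improved, unchanged and deteriorated, out of the 10 randomised. A separate category is better than relabelling these people as *deteriorated*: that class is defined by questionnaire change, and for someone removed mid-Phase 3 the last questionnaire precedes the app and cannot show worsening on it.
3. Keep SUDS ratings up to removal in the plots. Keep them in the baseline-versus-intervention time series where the minimum of 20 points per phase in Time Series Analysis is met. This needs a stated exception to the Data Exclusion minimums for these participants.

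The cost is some wording and slightly more reporting, with no new data collection. Results per app may look less favourable.
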